### Analysis

To address Aim 1, we will analyse data collected by both peer role models and project staff when conducting daily activities in the field. Simple descriptive data analysis will be used to answer this aim, such as counts of marketing materials distributed, counts of eligible young women introduced to project staff by peer role models and screened eligible. However, our primary analysis will test the hypothesis that the YWHC will reduce the primary outcome (sexual risk behaviour) as well as AOD use and victimisation relative to standard HCT (Aim 2: Hypothesis 1).

To test the efficacy of the intervention on each of these outcomes, we will use a standard intention-to-treat approach by including all participants as assigned to their study arm, regardless of their intervention exposure. The study design, which is longitudinal and clustered by community, creates an inherent multilevel structure, thereby introducing nonindependence. Consequently, our analytic strategy will be based on generalised linear mixed models, as use of hierarchical or multilevel mixed models allows for clustering due to community-level randomisation and repeated measures within individuals over time (at 6- and 12-month follow-up). Primary models will include a covariate for study arm, adjust for the baseline level of the outcome (e.g., heavy alcohol use), and account for community- and individual-level clustering. We will evaluate intervention effects individually at the two time points, initially by calculating proportions of the primary outcomes in the two randomised groups, with 95% confidence intervals. For multivariable modelling of intervention effects, we will use logit, Poisson, and linear regression approaches, as appropriate.

We will also test Hypothesis 2, which posits that the young women’s comprehensive HCT programme will improve the secondary outcome—access to HIV, STI, antenatal and reproductive health services—relative to standard HCT, using a similar data analysis approach. We will use a standard intention-to-treat analysis by including all participants as assigned to their study arm, regardless of their intervention exposure. The primary outcome of improved access will be operationalised in two ways: (1) a dichotomous measure of whether services were accessed (any and by type of service); and (2) a count of the number of times services were used during the 12-month follow-up period.

As described above, the initial test of the hypothesis that adolescent women in the YWHC intervention arm—as compared with adolescent women in the standard HCT arm—will be more likely to seek reproductive health services over 12 months, will be conducted with a model that includes a main (fixed) effect for intervention arm, a baseline measure of previous use of reproductive health services, and a random effect for community. We will conduct an exploratory analysis that includes potential effect modifiers and mediators—such as family connections, neighbourhood gang activity, and housing instability—to assess which interpersonal and structural factors might influence the YWHC intervention’s effects on access to HIV and other services.

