### Cluster creation and selection

Two geographic areas were selected for the study, one predominantly Coloured (of mixed race ancestry) and the other predominantly Black African. These areas comprise numerous distinct communities that characterise race, population size, area size, and socioeconomic status. Consequently, each community constituted a potential cluster, with large communities subdivided into multiple clusters that yielded 48 clusters across the two geographic areas.

Clusters were selected for inclusion in the study using the following criteria:There must be natural buffers between clusters; for example, at least two streets apart.The predominant race/ethnicity in the cluster must be 90% of the residents or higher.Very small clusters that could not generate the target sample size per cluster were excluded; for example, natural clusters with four or fewer small streets.

Clusters deemed outliers from other clusters were excluded; for example, high socioeconomic status in comparison to similar communities.

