### Cluster randomisation

We selected 12 clusters for each of the two geographic areas. Within each block of 12, clusters were randomised to one of the two arms, with equal allocation. Additionally, 5 replacement clusters were selected (3 within the Coloured geographic area and 2 within the Black African geographic area). These replacement clusters will be used if any of the selected clusters are deemed unusable prior to conducting outreach and recruitment in a specific cluster. At times, gangs are very violent, making outreach and recruitment dangerous, even during the day. If this persists in a community, it will need to be replaced for the purposes of this study.

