### Sample size and power

#### Power considerations for Aim 2

This study proposes several primary outcomes for Aim 2, and the power analysis were conducted to ensure that the study was adequately powered to detect intervention effects on these key outcomes, such as proportion of condom use (see earlier description of primary and secondary outcomes). The assumptions for this analysis are based on past studies of the WHC in South Africa and the Young Women’s CoOp pilot efficacy study conducted in the United States. In past studies, the proportion of condom use has ranged from 0.3 to 0.6. For all power analysis, we assumed a two-sided test with α = 0.05, a power of 0.8, and an intracluster correlation coefficient (ICC) estimate of 0.01. Based on these parameters, with a sample size of 225 per intervention arm at 12-month follow-up (an expected 90% follow-up) and 24 clusters, the minimal detectable difference is 0.13 for the outcome of condom use at the highest proportion of 0.6. For outcomes that may be less common overall, such as biologically confirmed HIV, we will be able to detect similar differences, ranging from 0.10 to 0.13.

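### Geographic area, the randomisation stratum, is missing from the stated models; if outcome levels still differ between areas after baseline adjustment, the tests are conservative and lose some power

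*Protocol article*

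**What the plan says.** The randomisation was stratified. Under Cluster randomisation, the protocol article says "We selected 12 clusters for each of the two geographic areas", and then "Within each block of 12, clusters were randomised to one of the two arms, with equal allocation". Each area therefore contributes 6 clusters to each arm. Cluster creation and selection describes the areas as "one predominantly Coloured (of mixed race ancestry) and the other predominantly Black African".

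The Analysis section states the model terms. For the primary outcomes, "Primary models will include a covariate for study arm, adjust for the baseline level of the outcome (e.g., heavy alcohol use"). The only further terms that sentence names are for clustering, by community and by individual. For Hypothesis 2, the model has "a main (fixed) effect for intervention arm, a baseline measure of previous use of reproductive health services, and a random effect for community". Neither statement includes geographic area, and nothing elsewhere in the article puts area into a model.

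Under Sample size and power, "we assumed a two-sided test with α = 0.05, a power of 0.8, and an intracluster correlation coefficient (ICC) estimate of 0.01". The calculation is made "with a sample size of 225 per intervention arm at 12-month follow-up (an expected 90% follow-up) and 24 clusters" and gives a minimal detectable difference of 0.13 at a condom-use proportion of 0.6. It does not say whether the ICC is within area or over all communities.

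**The concern.** Splitting each area 6:6 removes between-area differences from the true sampling variance of the arm contrast. An analysis that leaves area out does not know this. It sees communities in one area sitting higher than communities in the other, puts that spread into the community variance, and counts it as error against the arm effect. The estimate stays right, but its standard error is too large. Power and interval width suffer, and with 24 clusters and a detectable difference computed at exactly 80% power there is little to spare. The stratification has already been carried out, and the stated analysis does not collect its benefit.

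**Working it through.** **Inputs from the protocol article.** 225 analysed per arm; 24 clusters, 12 per arm and 12 per area; ICC 0.01; two-sided α 0.05; power 0.80; difference 0.13 at proportion 0.6.

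**Assumed, because the documents give no value.** The difference D in outcome prevalence between areas (a range is shown); within-person correlation 0.4 between baseline and follow-up; in steps 2 and 3, that the ICC of 0.01 is within area.

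**1. The plan's own figure.** Cluster size is 450/24 = 18.75. Design effect = 1 + (18.75 − 1) × 0.01 = 1.1775. Effective size per arm = 225/1.1775 = 191.1. Solving the two-proportion power formula upward from 0.6 gives 0.1346, which rounds to the stated 0.13. The figure reproduces.

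**2. Effect of a gap D that remains after any baseline adjustment.** This is a cluster-level linear approximation to the planned mixed model, with 0.60 against 0.73.

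- Variance of the arm contrast with area balanced: V = [0.60 × 0.40 + 0.73 × 0.27 − 2(D/2)²]/225 × 1.1775.
- Variance of one cluster mean: s² = V × 12/2 = 6V.
- Without an area term, 24(D/2)² is added to the residual sum of squares on 22 degrees of freedom, so the estimated variance is inflated by 1 + 24(D/2)²/(22 s²).

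For D = 0.20: V = (0.24 + 0.1971 − 0.02)/225 × 1.1775 = 0.00218; s² = 0.0131; inflation = 1 + 0.24/(22 × 0.0131) = 1.83.

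| Residual gap D | Variance inflation | Power with area | Power without area | Type I error without area |
|---|---|---|---|---|
| 0 | 1.00 | 0.736 | 0.739 | 0.050 |
| 0.05 | 1.05 | 0.738 | 0.724 | 0.045 |
| 0.10 | 1.20 | 0.741 | 0.678 | 0.033 |
| 0.15 | 1.46 | 0.747 | 0.603 | 0.019 |
| 0.20 | 1.83 | 0.756 | 0.501 | 0.009 |

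Type I error is never above 0.05.

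**3. Allowing for the planned baseline adjustment.** If the gap is present at baseline as well, a baseline slope of about 0.4 leaves roughly 1 − 0.4 = 0.6 of it: a raw gap of 10 points becomes about 6, and one of 20 becomes about 12. Simulation (12 clusters per arm, 19 per cluster, within-area ICC 0.01, difference 0.13, correlation 0.4, 6,000 to 8,000 trials per scenario) gives:

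| Raw gap | Power without area | Power with area | Loss |
|---|---|---|---|
| 10 points | 77% | 79% | 2 |
| 20 points | 72% | 80% | 8 |

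A separate simulation of 4,000 trials per scenario gave 77% against 80%, and 72% against 82%, so the losses are known to within a point or two. Type I error without area at 20 points was 2.6%. With no baseline adjustment, which is the limit where baseline predicts nothing, a 20-point gap gave 47% against 70%.

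**4. If the ICC of 0.01 is instead the total over all communities.** Area contributes about (D/2)²/(0.6 × 0.4) to the ICC. Setting this to at most 0.01 gives D ≤ 2√0.0024 = 0.098. On this reading the gap is at most about 10 points. Without baseline adjustment, power without area stays at 0.74 for gaps of 0, 5 and 8 points; with area it is 0.74, 0.76 and 0.79.

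**The case against.** The article is a condensed account, and an unseen analysis plan might list stratification covariates. The primary-model sentence is a summary: it names no time term either, although it covers two follow-up visits. The Hypothesis 2 model is called an initial test. This is fair as far as it goes, and nothing in the article excludes area. But the article chose to state its model terms, and the terms it states do not match the randomisation it describes, so the point is more than a detail left out.

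The size is open to a stronger objection, and most of that stands. No area-specific rates are given. All communities are economically disadvantaged and eligibility is narrow, which may limit differences between areas. Baseline adjustment is planned, so the unadjusted losses in step 2 apply only to the part of a gap that survives it. If the ICC of 0.01 is a total, leaving area out does not erode the planned power; it gives up a modest gain.

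A reader might also infer that the areas were picked to differ in socioeconomic setting. The article does not say so: it distinguishes the areas by predominant population group and excludes socioeconomic outliers among clusters.

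**Conclusion.** The mismatch holds: area is the randomisation stratum and is absent from both stated models. The consequence is one of efficiency only. If a gap between areas survives baseline adjustment, standard errors are too large and the test is conservative.

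The loss is negligible for a residual gap below about 5 points. With baseline adjustment at an assumed correlation of 0.4 and a within-area ICC of 0.01, it is about 2 power points for a raw gap of 10 points and about 8 for one of 20. It is larger for outcomes that baseline predicts poorly.

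A reader might infer that the results would be biased, that false positives would rise, that the trial is seriously underpowered, or that the ICC of 0.01 is wrong for the fitted model. The documents support none of these. The calculations show type I error at or below 0.05, large losses need gaps that nothing in the article establishes, and the ICC may be either within area or total. This is an inexpensive improvement, not a defect that invalidates the analysis.

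**What to change.** Add geographic area, as a two-level fixed effect for the randomisation stratum, to the primary models and to the Hypothesis 2 and other secondary models. State under Sample size and power whether the ICC of 0.01 is within area or total.

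The cost is a line of wording in each place and one degree of freedom. If the areas do not differ at all, power moves from 0.739 to 0.736, about 0.3 points. No new data are needed: the area of every cluster is known, and the replacement clusters are also listed by area. The article gives the trial status as enrolling, so the change can be made before outcomes are analysed. How denominator degrees of freedom are set in the logit, Poisson and linear models is a separate choice that this point does not prescribe.

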## Methods/Design

### Objectives

One aim of this study is to train and evaluate adolescent peer role models contracted from the government to market and conduct community outreach with established outreach workers to recruit 500 out-of-school adolescent women who use AODs, and to cofacilitate the YWHC. Another aim is to test the efficacy of the YWHC for reducing AOD use, victimisation, and sexual risk behaviour (primary outcomes) and improving access to effective treatment and support services through linkages to care (substance abuse rehabilitation, HIV, sexually transmitted infections [STIs], antenatal and reproductive health services as secondary outcomes) relative to standard HCT for adolescent women.

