### Study activities by arm

#### Intervention arm

Participants in the intervention arm take part in all of the activities described above for the control arm. Additionally, they are asked to attend two group workshops of the YWHC. Participants are contacted by staff to confirm attendance to the intervention workshops within a week of their intake appointment. Up to eight participants form a workshop group.

The intervention consists of two group workshops lasting approximately 2 h each, with each workshop containing several modules and exercises (see Table 2 for a detailed summary of the workshop content). Workshops are conducted approximately 7 to 10 days apart. Workshop 1 covers developmental issues, AODs, pregnancy and parenting, gender issues, violence, communication, and negotiation. Workshop 2 covers sex and risk, HIV and other STIs, sexual risk reduction (including male and female condoms), and safer sex negotiation with partners. The modules include voices and quotes from the formative focus group discussion participants who willingly shared their stories. Both workshops end with each participant working toward developing a personalised risk-reduction action plan. As with the intake, active referrals are offered where appropriate.

**Table 2 Tab2:** Young Women’s Health CoOp Workshop Content

Workshop 1		
Topic	Slides	Activity
Becoming a Woman	• Life Stages of Development • Who Influences You • Growing up and Maturing • How Can You Be in Control? • Becoming Your Own Woman • Making Decisions and Never Too Late to Change	
Alcohol and Other Drug (AOD) Use	• AOD Use Compromises Young Women • Intersecting Risks • Using Alcohol and Other Drugs • Types of AODs and Risks • Effect of AOD Use on Sex • Risks of Using AODs • Reducing AOD Risks	Drug Type Activity
Pregnancy and Parenting	• Breastfeeding • Teen Parenting Challenges • Tips for Being a Good Parent	
Communication and Negotiation	• Learning How to Communicate and Negotiate With Others • Understanding Conflict • Conflict Resolution Steps • Ground Rules for Conflict Resolution	Conflict Resolution Role-play
Gender and Power	• Inequality and Lack of Power • Types of Boyfriends • Getting Away from Bad Boyfriends • Gangs and Issues • When Things Go Wrong • Response to Danger with Guys	
Violence	• Intersecting Risks • Rape and Sexual Assault • Truths and Myths of Rape • Safety Tips When Going Out	Truths and Myths of Rape

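### Workshop groups in the intervention arm are missing from the stated clustering levels: a modest loss of power either way, and a mild rise in type I error only if groups mix communities

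*Protocol article*

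**What the plan says.** - **Delivery.** Intervention participants attend two workshops of about two hours each: "Up to eight participants form a workshop group" (Intervention arm). The Control arm section describes standard HIV counselling and testing, with no groups.
- **Randomisation.** Communities are the randomised units, 12 in each of two areas: "Within each block of 12, clusters were randomised to one of the two arms, with equal allocation" (Cluster randomisation). This gives 12 communities per arm.
- **Analysis.** The primary generalised linear mixed models adjust for baseline and "account for community- and individual-level clustering". The service-access model has a random effect for community.
- **Power.** The calculation takes "an intracluster correlation coefficient (ICC) estimate of 0.01" and, "with a sample size of 225 per intervention arm at 12-month follow-up (an expected 90% follow-up) and 24 clusters", concludes that "the minimal detectable difference is 0.13 for the outcome of condom use at the highest proportion of 0.6".
- **Group formation.** The article does not say whether a workshop group comes from one community or several. It does say that participants are brought to a field site for study activities (Intake assessment).

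**The concern.** Women treated in the same workshop share discussion, role-play and a facilitator, so their outcomes may be correlated beyond what a shared community explains. That correlation can arise in one arm only. The Analysis section argues from non-independence and then lists its levels, but leaves out the one that the intervention itself creates.

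Two things could follow. If groups draw women from several communities, outcomes become correlated across the randomised units of the intervention arm. A community effect cannot represent this, so the standard error of the arm effect is too small. If groups sit inside a community, the correlation shows up as extra spread between intervention communities. The model sees that spread, so the test stays close to its nominal level, but precision is lower than the power calculation assumed.

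**Working it through.** **Inputs from the Protocol article.** Two-sided α 0.05 and power 0.80 ("we assumed a two-sided test with α = 0.05, a power of 0.8"); ICC 0.01; 225 per arm at 12 months; 12 communities per arm; reference proportion 0.60; groups of up to 8. Recruitment is 500 ("recruit 500 out-of-school adolescent women who use AODs"), so 250 per arm, and 250 × 0.9 = 225.

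**Assumptions, not in the documents.** Workshop ICC ρ (extra correlation within a group, beyond community) of 0.02 to 0.10. Two delivery scenarios: (a) groups of 8 with every woman attending; (b) groups of 6 with 80% attending.

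**Step 1: reproduce the stated figure.** Cluster size m = 225/12 = 18.75. Design effect D = 1 + 17.75 × 0.01 = 1.1775. With unpooled variance, d solves

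d = (1.960 + 0.842) × √{[0.60 × 0.40 × D + (0.60 + d)(0.40 − d) × D] / 225}.

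This gives d = 0.134, which agrees with the stated 0.13 after rounding. Power at exactly 0.13 is 0.78 before any workshop effect is considered.

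**Step 2: add the workshop correlation to the intervention arm.** The intervention design effect becomes D_I = 1.1775 + kρ, where k = 8 − 1 = 7 in scenario (a) and k = 0.8 × (6 − 1) = 4 in scenario (b). D_I replaces D in the second term of the formula.

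| ρ | (a) D_I | (a) detectable difference | (a) power at 0.13 | (b) D_I | (b) detectable difference |
|---|---|---|---|---|---|
| 0 | 1.1775 | 0.134 | 0.78 | 1.1775 | 0.134 |
| 0.02 | 1.3175 | 0.137 | 0.75 | 1.2575 | 0.136 |
| 0.05 | 1.5275 | 0.142 | 0.72 | 1.3775 | 0.138 |
| 0.10 | 1.8775 | 0.149 | 0.68 | 1.5775 | 0.143 |

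A pooled-variance formula gives values up to about 0.004 larger (0.135 with no group effect; 0.153 at ρ = 0.10 in scenario (a)).

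**Step 3: type I error if groups mix communities.** With random mixing, the spread between community means still reflects D, not D_I. The true standard error therefore exceeds the estimated one by √[(D + D_I)/(2D)].

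- Scenario (a): ratios 1.029, 1.072 and 1.139 at ρ = 0.02, 0.05 and 0.10. The error rate 2 × P(Z > 1.96/ratio) is 0.057, 0.067 and 0.085; with a t reference on 22 df it is 0.056, 0.066 and 0.082.
- Scenario (b): ratios 1.017, 1.042 and 1.082. With t on 22 df the error rate is 0.054, 0.059 and 0.068.

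Null simulations agree in order of size. Those below are at ρ = 0.05 and 0.10, 20,000 runs per setting, with a continuous outcome in the second:

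- 12 communities of 20 per arm, mixed groups of 8: 0.069 and 0.079 for a t test on community means; 0.057 and 0.066 for a random-intercept estimator with t on 22 df.
- 12 communities of 18 per arm, mixed groups of 6: 0.064 and 0.074 for the community-only mixed model with z; 0.051 and 0.059 with t on 22 df.

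**Step 4: type I error if groups are nested in communities.** In the second simulation setting, the t test on community means gave 0.050 and 0.053. The community-only mixed model gave 0.055 and 0.062 with z, and 0.043 and 0.049 with t on 22 df. The community term absorbs most of the group variance.

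**The case against.** The strongest reply is that the randomised unit is already in the model. If groups sit within a community, which the article may simply not have had room to say, the test needs no rescue. Several features make limited mixing plausible: outreach is described cluster by cluster, workshops follow within about a week of intake, and the two areas differ in population and home language. None of them settles it. This part stands: a reader might infer that the planned analysis is invalid or that its false-positive rate exceeds 5%, and the documents do not support that. It would need groups that cross communities, which the text neither states nor rules out.

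The size is also open to challenge. Eight is a maximum, some women will not attend, and intention-to-treat keeps non-attenders in the arm without a group effect. The exposure is two sessions, then individual case management, with outcomes at 6 and 12 months, so lasting group correlation may be small. At a workshop ICC of 0.02 the detectable difference moves by only about 0.002 to 0.003. If the planned 0.01 was meant to include workshop correlation, part is already covered, though the article does not say so. The gap between power of 0.78 and 0.80 at exactly 0.13 comes from rounding and should not be charged to the workshops.

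What survives is narrower. The article does name its clustering levels, so this is more than detail left to an analysis plan, and a workshop correlation of exactly zero is an assumption that it does not defend.

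**Conclusion.** The point holds in a limited form, as a cheap improvement. The stated model and power calculation omit a level of clustering that exists in the intervention arm only.

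- **Validity.** Essentially intact if groups are nested in communities (0.05 to 0.06). If groups mix communities, type I error is about 0.05 to 0.08 for workshop ICCs of 0.02 to 0.10; the upper end needs full groups, full attendance and the largest ICC.
- **Power.** The detectable difference upward from 0.60 goes from 0.134 to about 0.136 to 0.149 in either case. The direction is certain for any positive workshop ICC not already contained in the 0.01. The amount is not, because the documents give no such ICC.

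A reader might take the stated 0.13 to be materially wrong. It is not: it reproduces after rounding, and the plausible shift is at most about one and a half percentage points.

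**What to change.** 1. Record each intervention participant's workshop group, separately for each workshop if membership changes, and the community make-up of each group. The trial is listed as enrolling, so this is easier now than to reconstruct later.
2. If any groups cross communities, add a random effect for workshop group in the intervention arm only (controls and non-attenders as singletons) to the community and individual effects. If all groups are nested, keep the community model with small-sample degrees of freedom and run the partially nested model as a sensitivity analysis.
3. Restate the detectable difference from 0.60 as about 0.13 to 0.15 over workshop ICCs of 0 to 0.10.

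**Cost.** One or two identifier variables and a few lines of analysis text. One more variance component must be estimated from about 31 or more small groups (250/8 = 31.25), and it may be poorly estimated, particularly for binary outcomes. The stated detectable difference becomes slightly less favourable. Randomisation, recruitment and delivery do not change.

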**Methods:**

This cluster-randomised trial is enrolling participants into two arms: a control arm that receives standard HCT, and an intervention arm that receives the YWHC. Participants are enrolled from 24 economically disadvantaged communities in Cape Town, South Africa. These geographically distinct communities serve as clusters that are the units of randomisation. This study uses adolescent peer role models and research field staff to recruit marginalised adolescent women. At baseline, participants complete a questionnaire and biological testing for HIV, recent AOD use, and pregnancy. The core intervention is delivered in the month following enrollment, with linkages to health services and educational programmes available to participants throughout the follow-up period. Follow-up interviews and biological testing are conducted at 6 and 12 months post enrollment.

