#### Intake assessment

Participants are transported to a secure field site for all study activities. After final eligibility is determined through a rescreening, consent and/or assent is obtained, participants take a breathalyser test for recent alcohol use, locator information is collected, and a photograph of the participant is taken (which is returned at the final appointment). At this first appointment, participants complete the baseline questionnaire via computer-assisted personal-interviewing (CAPI) technology, and audio computer-assisted self-interviewing (ACASI) in their home language (English, Afrikaans, or isiXhosa) for sensitive topics, such as experiences of abuse. Staff then collect biological specimens to conduct pregnancy testing, screening for recent drug use, and rapid HIV testing. A urine specimen sample is collected to perform rapid tests to detect metabolites of recent use of cocaine, methamphetamines, amphetamines, opioids, ecstasy, and marijuana via a 5-panel drug screening test. Methaqualone (Mandrax) is measured through a separate urinalysis test. Two rapid tests are conducted for HIV testing; if a participant has a positive test result for either test, she receives a third test and posttest counselling in accordance with the national South African standards. If two tests show a positive HIV result, the participant is considered to have a positive test. All staff undergo training for biological specimen collection and are certified to conduct rapid HCT. All positive HIV screening determinations or positive test results for pregnancy are referred to the local health clinic regardless of study arm. For other services needed, participants in the intervention arm receive active referrals, whereas participants in the HCT control arm receive passive referrals.

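### The stated Hypothesis 2 model omits the baseline pregnancy and HIV results that trigger clinic referral in both arms; the test stays valid but gives up precision, mainly for antenatal access

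*Protocol article*

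**What the plan says.** **The model.** The Analysis section says the Hypothesis 2 approach is similar to that for Hypothesis 1, where "Primary models will include a covariate for study arm, adjust for the baseline level of the outcome". For the initial test on reproductive health services over 12 months it names the terms: a fixed effect for arm, "a baseline measure of previous use of reproductive health services, and a random effect for community". Other factors appear only in an exploratory analysis of modifiers and mediators, whose examples include neither pregnancy nor HIV.

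**The outcome.** Hypothesis 2 concerns access to HIV, STI, antenatal and reproductive health services. It is analysed as any access, as access by type of service, and as a count.

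**The baseline results.** The abstract states: "At baseline, participants complete a questionnaire and biological testing for HIV, recent AOD use, and pregnancy". Under Intake assessment: "All positive HIV screening determinations or positive test results for pregnancy are referred to the local health clinic regardless of study arm". Under Control arm, other referrals are made when the participant asks; pregnancy and a positive HIV screen are the stated exceptions.

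**The concern.** The protocol itself ties the two omitted results to the outcome. In the control arm they are the exception to referral on request. Antenatal access largely presupposes a pregnancy, and HIV care presupposes an infection. Previous use of reproductive health services recovers part of this information, but a pregnancy or infection first found at intake has no matching earlier use.

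Leaving a known predictor out of the model leaves explainable variation in the error term. Randomisation is blocked only by geographic area, with 12 clusters per arm, so the share of positive women will differ somewhat between arms by chance. That adds noise to the estimated access difference. At stake is the precision of a secondary analysis, not its validity.

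**Working it through.** **1. The plan's own figure.** The inputs come from Sample size and power: "we assumed a two-sided test with α = 0.05, a power of 0.8", "an intracluster correlation coefficient (ICC) estimate of 0.01", and "with a sample size of 225 per intervention arm at 12-month follow-up (an expected 90% follow-up) and 24 clusters".
- Mean cluster size at 12 months: 225/12 = 18.75.
- Design effect: 1 + (18.75 − 1) × 0.01 = 1.1775.
- Effective n per arm: 225/1.1775 = 191.1.
- Pooled two-proportion test: the detectable difference upward from 0.60 at 80% power is 0.1346.

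The article states "the minimal detectable difference is 0.13 for the outcome of condom use at the highest proportion of 0.6", so the figure reproduces within rounding; power at exactly 0.60 v 0.73 is 77.0%. No power figure is given for service access.

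**2. Precision from one binary covariate, any-service access.** Assumptions, none from the documents: access p = 0.3 to 0.5, share positive at intake q = 5% to 30%, and access higher by d = 0.1 to 0.4 among positives.
- R² = q(1 − q)d² / [p(1 − p)].
- Smallest case (q = 0.05, d = 0.1, p = 0.5): 0.0475 × 0.01/0.25 = 0.002.
- Largest case (q = 0.3, d = 0.4, p = 0.3): 0.21 × 0.16/0.21 = 0.16.
- Adjusted variance = (1 − R²) × unadjusted variance. Starting from 80% power, adjustment gives 80.1% to 86.4%. A detectable difference of 0.13 becomes 0.130 to 0.13 × √0.84 = 0.119.

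**3. With previous use already in the model.** Simulation of 24 clusters of 19 women, cluster-level t-test on 22 df, 4,000 runs. Assumed: access 40%, intervention effect 14 points, previous use 30% and raising access by 20 points, ICC 0.01. The ranges below cover previous use unrelated to, and related to, the intake result.

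| q | d | Power, previous use only | Power, intake result added |
|---|---|---|---|
| 0.1 | 0.2 | 76.7–77.5% | 77.2–77.9% |
| 0.2 | 0.2 | 77.2–77.9% | 78.1–78.9% |
| 0.2 | 0.4 | 76.0–77.9% | 80.4–81.2% |
| 0.3 | 0.4 | 77.6–78.8% | 83.1–83.5% |

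The gain is 0.4 to about 1 point at d = 0.2, and about 3 to 6 points at d = 0.4.

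**4. Antenatal access.** Same layout, with the baseline pregnancy result added to a model without covariates. Assumed rates:

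| Pregnant at intake | New pregnancies among others | Access if pregnant, control v intervention | Power without | Power with | SD of estimate |
|---|---|---|---|---|---|
| 10% | 10% | 50% v 90% | 64% | 79% | 0.0318 → 0.0260 |
| 10% | 5% | 40% v 90% | 73% | 91% | 0.0270 → 0.0209 |
| 20% | 10% | 50% v 80% | 61% | 81% | 0.0362 → 0.0286 |

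A second set of assumptions (10–20% pregnant; access 60% v 85% if pregnant, 5–8% v about 6.5–10% otherwise) moved power from 20–35% to 31–57%.

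**5. Validity and imbalance.** With no effect, rejection in the antenatal simulation was 5.5% without and 5.1% with the covariate. The any-access null runs were also near 5% for both models. The SD of the between-arm difference in share positive is √[2q(1 − q) × 1.1775/225]: 3.1 points at q = 0.1 and 4.7 at q = 0.3. Multiplied by d, this moves the unadjusted access difference by an SD of 0.3 points (0.031 × 0.1) to 1.9 points (0.047 × 0.4).

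**The case against.** The strongest reply is that nothing here is misstated. Adjusting for the baseline value of the outcome is standard and valid. The article calls the listed model the initial test, mentions further multivariable modelling without closing the covariate list, and condenses a fuller plan that is not shown and may already include these covariates. This stands as a limit on the point: it bears on the model the article states, not on what an unseen plan may add. It does not dispose of the point, because the article names the terms of that test and its own referral procedure identifies two collected predictors that are absent.

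Three stronger readings are tempting and are not supported.
- **Bias.** A reader might infer that chance imbalance biases the access comparison. It does not; it is random error that the confidence interval already covers.
- **A large loss for any-service access.** One can assume 90% access among positives in both arms and 35% v 48% in the others. With 10%, 20% or 30% positive, power is then 60%, 50% or 40% unadjusted and 65%, 57% or 49% adjusted. But that comparison leaves out the planned previous-use covariate and fixes an extreme gap. The fall across prevalences arises mostly because no effect is assumed among positives: giving them the same 13-point effect (77% v 90%) keeps unadjusted power at 68–71%. With 60% access among positives the gain from adjustment is only about 1 point.
- **Hypothesis 1.** A link from baseline pregnancy to condom use or drinking is conceivable, but no passage states one.

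Two technical cautions also stand. In by-type logit models the intake result may nearly determine the outcome, so separation is possible. Adding covariates to a logit model also changes the conditional odds ratio being estimated.

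**Conclusion.** The point holds as a matter of efficiency in Hypothesis 2. The stated model leaves out two baseline results that the protocol's own procedures make probable drivers of antenatal and HIV service access. Under the assumed rates the cost is under 1 to about 6 points of power for any-service access with previous use in the model, and about 10 to 20 points for antenatal access.

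These sizes rest on assumed prevalences and access rates. The antenatal runs also contain no previous-use term, and all the simulations use a linear cluster-level test rather than the planned mixed models. The direction is well supported by the documents; the exact size cannot be derived from them. That every woman has both results is the planned procedure; the article does not describe refusals or missing tests.

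**What to change.** - **Any-access and count models:** prespecify the baseline pregnancy result and the baseline HIV result as fixed effects, alongside arm, previous use and the community random effect.
- **Antenatal-access model:** add the baseline pregnancy result.
- **Other by-type models:** include either result only where cells are not so sparse that separation occurs. At 10% positive, a cluster of 18.75 women holds about two positives.
- **Reporting:** give a standardised risk difference beside any odds ratio, and keep the current model as a sensitivity analysis.
- **Hypothesis 1 models:** leave as they are.

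The cost is a short addition to the analysis text, one or two degrees of freedom per model, and a conditional odds ratio with a changed meaning. No new data are needed. The article gives the trial status as enrolling; the change should be made before outcomes are seen, since covariates added after an imbalance is noticed would be open to challenge.
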